## Methods/Design

### Study design

A multicenter, prospective observational cohort study in which patients starting treatment with erlotinib will be followed for a period up to 16 weeks. At baseline and in weeks 3-4, 8-9, 12 and 15-16, patients will be asked to fill out a questionnaire. Furthermore, in weeks 3-4, 8-9 and 15-16, blood samples are collected, which will be analysed for plasma concentration of erlotinib. Adherence will be measured using a medication event monitoring system (MEMS). Information from the physician will be retrieved from the patient treatment file.

### Ethics

The protocol was approved by the Medical Ethics review board of the VU University Medical Center, Amsterdam, The Netherlands.

### Recruitment and consent

Patients will be recruited by the Departments of Pulmonalogy from twelve hospitals in the Netherlands. After the patient and doctor have decided on treatment with erlotinib, patients will be informed about the study and will receive written information to take home. Within two days the researcher will contact the patient by phone to further inform the patient of the study and to ask for his/her consent. If the patient decides to participate in the study, he or she will sign the informed consentform.

### Inclusion criteria

Patients with advanced NSCLC under treatment in one of the participating hospitals starting with the use of erlotinib can be included. Patients younger than 18 years and those with insufficient knowledge of the Dutch language will be excluded. According to the sample size calculation (see Statistics) a number of 65 patients will be enrolled.

### Measurements

Several methods are used to determine the variables. Most information is collected directly from patients: they will fill out questionnaires, will use an electronic monitoring pill-container and will donate blood samples. Furthermore, medical information will be retrieved from the patients' file.

#### Questionnaires

The patients will be asked to fill out five questionnaires spread over 16 weeks. The first questionnaire (t = 0) contains questions on patient characteristics, smoking, co-medication, side-effects, quality of life, and patients beliefs and attitude towards disease and medication. In weeks 3-4, 8-9 and 15-16 patients will be asked to fill out an elaborate questionnaire containing questions determining the adherence behaviour, side-effects, dose adjustment, co-medication, quality of life, and patients beliefs and attitude towards disease and medication. In week 12 patients are asked to fill out a short questionnaire containing only questions determining the adherence behaviour, side effects, and dose adjustment. Discontinuation and reasons for discontinuation will be asked in a short questionnaire when a patient stops the erlotinib treatment prematurely.

The questionnaires contain the following items:

1. MARS (Medication Adherence Report Scale) [40,41]. This questionnaire contains statements about adherence behaviour.

2. Nature and grade of the side-effects in a five-point scale.

3. Quality of life measured with SF-12 Health Survey [42,43]. The SF-12 is a short version of the SF-36 and is a validated method to measure quality of life.

4. Attitude towards disease measured with Brief Illness Perception Questionnaire (Brief IPQ) [21]. The Brief IPQ is a validated method to measure the attitude towards disease.

5. Beliefs and attitude towards medicines measured with Beliefs about Medicines Questionnaire (BMQ) [22]. The BMQ is a validated questionnaire. It is divided in two parts, the BMQ general and the BMQ specific. BMQ general measures the patient's beliefs and attitude towards medicines in general. The BMQ specific is specified for erlotinib.

6. Patient characteristics: date of birth, gender, socio-economic status and smoking (current smoking and never/previous smoking).

7. Dose adjustments by the patient. Dose adjustments introduced by the doctor will be derived from the patient file.

8. Co-medication.

9. Discontinuation and reasons for discontinuation. Discontinuation is also derived from the patient file.

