### Pharmacokinetics

Hidalgo et al [32] have suggested that an erlotinib plasma concentration of 0.5 μg/ml would be sufficient for relevant antiproliferative activity. Peak concentrations (Cmax) of erlotinib of 1.737 ± 0.777 μg/ml are reached 2.44 ± 1.94 hour (Tmax) after administration of 150 mg a day. Erlotinib has a plasma volume of 233 L and is for 95% bound to plasma proteins like albumine and α1-acid-glycoprotein. The plasma elimination half-life is approximately 36 hours [36]. Erlotinib is mainly metabolized by the liver (90%), only a small part is excreted by the kidneys (9%). It is primarily metabolized by cytochrome P450 3A4 (CYP3A4) and in a lesser extent by CYP1A2, It is a substrate of the multi-drug transporter ATP-binding cassette transporter ABCG2 [37].

Several drug interactions, smoking and food may influence plasma concentrations of erlotinib. Drugs that increase the pH of the upper gastrointestinal tract may alter the solubility of erlotinib, thereby reducing its bioavailability. Inhibitors or inducers of CYP3A4 and CYP1A2 influence the metabolism of erlotinib, which may result in increased or decreased plasma concentrations [31] Smoking results in a significantly lower plasma concentration [38]. When erlotinib is taken together with food the bioavailability of erlotinib increases almost two-fold [39]. It is therefore advised by the manufacturer to take erlotinib at least one hour before or two hours after a meal [31]. Serum total bilirubin, serum α1-acid glycoprotein, serum albumin, creatinine clearance and gender are significant co-variables that explain interindividual variability for clearance [36].

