#### Blood sample and laboratory test

A plasma sample will be collected at visits of the patient at week 3-4, 8-9 and 15-16. This blood sample will be drawn simultaneously with the regular treatment's related blood sampling. At these visits patients are asked when they had their last meal and at what time they took their last erlotinib medication. Patients are supposed to take erlotinib at least one hour before or two hours after a meal [31]. Adherence to the instruction will be taken into account in the analysis of the study results.

Apart from that, the time of the blood sample will be documented. Plasma concentrations of erlotinib will be analyzed by LC-MS/MS. The pharmacokinetic parameters AUC, C_max _and C_through _will be derived using the pharmacokinetic model as described by Lu et al [36]. The concentration ratio (CR) is defined as the measured erlotinib concentration divided by the mean population erlotinib concentration that is predicted by the model. To calculate the AUC, C_max_, C_through _and CR the following covariates are measured and used as input for the model: gender, serum albumin, serum total bilirubin, serum α1-acid glycoprotein, calculated creatinine clearance and smoking status [36]. The calculated AUC, C_max_, C_through _and CR will be compared with the data on adherence from the questionnaires and the electronic monitoring system to study the relationship between adherence and the plasma concentration of erlotinib.

Patients are asked about their co-medication in the questionnaires. The data on co-administration of inhibitors of CYP1A2 and CYP3A4, inductors of CYP3A4 and antacids will be examined as covariables.

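### Smoking status feeds the concentration model at weeks 3-4, 8-9 and 15-16 but is listed only in the baseline questionnaire, so the concentration ratio can be wrong for patients whose smoking changes

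*Protocol article*

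**What the plan says.** All references are to the protocol article.

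- **Questionnaires, baseline.** "The first questionnaire (t = 0) contains questions on patient characteristics, smoking, co-medication, side-effects, quality of life". Smoking is recorded at two levels (current, or never/previous) and is grouped with date of birth, gender and socio-economic status as a patient characteristic.
- **Questionnaires, weeks 3-4, 8-9 and 15-16.** Patients receive an "elaborate questionnaire containing questions determining the adherence behaviour, side-effects, dose adjustment, co-medication, quality of life, and patients beliefs and attitude towards disease and medication". Co-medication is repeated; smoking is not listed. The week 12 form lists neither, but no blood is drawn then.
- **Blood sample and laboratory test.** Samples are taken at weeks 3-4, 8-9 and 15-16. The model inputs are gender, three serum measurements, "calculated creatinine clearance and smoking status". CR is the measured concentration divided by the population mean that the model predicts. The questions named for the sampling visit are the last meal and the time of the last erlotinib intake.
- **Background, Pharmacokinetics, on smoking.** "Smoking results in a significantly lower plasma concentration". No size is given.
- **Co-medication.** The Background says "Inhibitors or inducers of CYP3A4 and CYP1A2 influence the metabolism of erlotinib", and also "Drugs that increase the pH of the upper gastrointestinal tract may alter the solubility of erlotinib". The laboratory section says that "inhibitors of CYP1A2 and CYP3A4, inductors of CYP3A4 and antacids will be examined as covariables".

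**The concern.** Smoking can change during 16 weeks of treatment, and the article itself says that it lowers the erlotinib concentration. If the only recorded status is the baseline one, the model can predict a smoker's concentration for a patient who has stopped, or a non-smoker's for one who has resumed. The prediction is the denominator of CR, so the whole modelled smoking effect would appear as unusually high or low exposure. The relationship between adherence and plasma concentration is part of the primary objective, and CR is one of the four derived measures to be compared with adherence. A status that was never collected cannot be recovered by a later analysis plan.

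The co-medication list raises a lesser question: it does not match the Background's account of which drugs alter concentration.

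**Working it through.** The plan states no figure on this point, so there is none to reproduce. The check sets the sections side by side and then works the possible error from the article's own definition of CR.

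**1. Is current smoking available at sampling?** Three sources could supply it.

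- Questionnaires at weeks 3-4, 8-9 and 15-16: smoking is not listed, while co-medication is.
- Questions at the sampling visit: only the last meal and the last intake are named.
- Patient file: disease characteristics, dose adjustments and discontinuation are listed, not smoking.

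The only listed source is the baseline questionnaire.

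**2. Error in CR for one patient whose status has changed.** Let f be the proportion by which smoking lowers the predicted concentration. The article gives no value, so f = 0.20 to 0.50 is an assumption.

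- Stopped but still coded current: the denominator is too small by (1 − f), so CR is multiplied by 1/(1 − f). This gives 1/0.80 = 1.25 up to 1/0.50 = 2.0.
- Resumed but still coded never/previous: CR is multiplied by (1 − f), which gives 0.80 down to 0.50.
- Status unchanged: the factor is 1, so there is no error.

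**3. Comparison with a missed dose.** With the article's half-life of about 36 hours, one omitted daily dose before a trough sample multiplies the concentration by 2^(−24/36) = 0.63, whose reciprocal is 1.59. The smoking error equals this when 1 − f = 0.63, so f is about 0.37. At f = 0.25 the factors are 0.75 and 1.33, a smaller error than a missed dose. At f = 0.50 they are 0.50 and 2.0, a larger one.

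**4. How many patients?** The article does not say how many patients change status. If 5%, 10% or 20% of the 65 did so (assumption), that is 65 × 0.05 = 3.25, 65 × 0.10 = 6.5 or 65 × 0.20 = 13, so roughly 3 to 13 patients.

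**5. Co-medication lists compared.**

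| Background | Covariables in the laboratory section |
|---|---|
| CYP3A4 inhibitors | present |
| CYP1A2 inhibitors | present |
| CYP3A4 inducers | present |
| CYP1A2 inducers | absent |
| drugs raising upper gastrointestinal pH | present as antacids, not defined |

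Co-medication is not among the model inputs, so neither difference can enter the denominator of CR. Both act only where co-medication is examined as a covariable.

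**The case against.** The strongest reply is that the smoking point rests on silence in a condensed article. The laboratory section says that the covariates are measured and used in the model, without saying when, and lists smoking beside serum values. A record at the sampling visit is compatible with that text, and the actual forms are not shown. This stands in part: the article nowhere says that baseline smoking status is carried forward. It does, however, set out the content of each questionnaire and the questions at the sampling visit, and none of them includes smoking after baseline.

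A reader might infer more than the article supports in four ways.

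- **That CR is in fact mis-adjusted.** The error arises only in patients whose smoking changes, and their number is unknown.
- **That the error is as large as the adherence signal.** This fails over part of the assumed range, below f of about 0.37. It also compares single patients and says nothing about the study result. The calculation is for CR alone; no error has been derived for AUC, Cmax or trough, which also use the measured concentration.
- **That the primary result is biased.** That needs a link between smoking change and adherence, which the article does not show. Without one, the error is mainly noise.
- **That several drug classes are dropped and CR suffers.** Only CYP1A2 inducers are clearly missing. Antacids may be loose wording for the wider group. Co-medication is collected at baseline and at all three sampling times, so any class can still be coded. The Statistics section also allows adjustment for unspecified potential confounders, so the list need not be exhaustive.

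**Conclusion.** The smoking point holds as a mismatch between what is collected and what the model needs. As listed, smoking is asked at baseline only but is used for samples at weeks 3-4, 8-9 and 15-16, so CR can be wrong for patients whose smoking changes in between. For such a patient, an assumed smoking effect of 20-50% gives a CR error of 1.25-2.0 fold upward after stopping, or a factor of 0.8-0.5 after resuming. The effect on the adherence analysis cannot be sized, because neither the smoking effect nor the share of patients who change is given. The correction is worth making because it is cheap and the missing status could not be reliably restored after data collection.

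The co-medication point holds in a narrower sense. CYP1A2 inducers are absent from the covariable list although the Background says that they matter, and antacids needs a definition. This concerns the later adjustment only, not CR, and can be settled at analysis.

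**What to change.** Add the current-smoking item to the questionnaires at weeks 3-4, 8-9 and 15-16, or to the questions asked when blood is drawn. State that the model uses the status recorded at that visit for that visit's sample. The cost is one extra question at three existing visits, with a slight added burden for patients.

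Separately, in the laboratory section, add CYP1A2 inducers to the covariables and define antacids to cover the drugs that raise upper gastrointestinal pH named in the Background, coded per visit. The co-medication data are already collected at each sampling time, so this costs one sentence on coding.

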#### Electronic monitoring system

Adherence will be measured using a medication event monitoring system (MEMS) [44]. Electronic monitoring systems use standard pill containers with a small electronic processor in the cap, to record the timing and frequency of bottle openings. Compared to other methods (e.g., assay, self-report, collateral report, prescription refills), electronic monitoring captures more of the dynamics of medication-taking behaviour [45]. In this study the Evalan Real Time Medication Monitoring (RTMM) is used.

#### Patient file

The following items are derived from the patient treatment file.

• Disease characteristics like disease stage and line of treatment.

• Dose adjustments

• Discontinuation and reasons for discontinuation

#### Blood sample and laboratory test

A plasma sample will be collected at visits of the patient at week 3-4, 8-9 and 15-16. This blood sample will be drawn simultaneously with the regular treatment's related blood sampling. At these visits patients are asked when they had their last meal and at what time they took their last erlotinib medication. Patients are supposed to take erlotinib at least one hour before or two hours after a meal [31]. Adherence to the instruction will be taken into account in the analysis of the study results.

Apart from that, the time of the blood sample will be documented. Plasma concentrations of erlotinib will be analyzed by LC-MS/MS. The pharmacokinetic parameters AUC, C_max _and C_through _will be derived using the pharmacokinetic model as described by Lu et al [36]. The concentration ratio (CR) is defined as the measured erlotinib concentration divided by the mean population erlotinib concentration that is predicted by the model. To calculate the AUC, C_max_, C_through _and CR the following covariates are measured and used as input for the model: gender, serum albumin, serum total bilirubin, serum α1-acid glycoprotein, calculated creatinine clearance and smoking status [36]. The calculated AUC, C_max_, C_through _and CR will be compared with the data on adherence from the questionnaires and the electronic monitoring system to study the relationship between adherence and the plasma concentration of erlotinib.

Patients are asked about their co-medication in the questionnaires. The data on co-administration of inhibitors of CYP1A2 and CYP3A4, inductors of CYP3A4 and antacids will be examined as covariables.

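### The last-meal and last-dose times asked at the visit do not in general show whether the last dose followed the meal instruction, and one dose says little about food exposure at a 36-hour half-life

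*Protocol article*

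**What the plan says.** The section Blood sample and laboratory test of the protocol article describes three sampling visits (weeks 3-4, 8-9 and 15-16). At these, "patients are asked when they had their last meal and at what time they took their last erlotinib medication". The rule against which the answers are to be judged is given next: "Patients are supposed to take erlotinib at least one hour before or two hours after a meal". The article then commits to using the result: "Adherence to the instruction will be taken into account in the analysis of the study results". The draw is tied to routine care ("This blood sample will be drawn simultaneously with the regular treatment's related blood sampling"), and "the time of the blood sample will be documented".

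The Pharmacokinetics section of the Background supplies the two figures that decide how much this matters: "When erlotinib is taken together with food the bioavailability of erlotinib increases almost two-fold", and "The plasma elimination half-life is approximately 36 hours".

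The article describes no other source of meal data. The items listed under Questionnaires contain no question on meal timing, the electronic monitor records bottle openings, and the Patient file items do not cover food. Food is also absent from the listed inputs to the pharmacokinetic model and from the co-medication covariables.

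**The concern.** Whether a dose followed the instruction depends on the meals on both sides of it: the rule is broken if any meal falls between 2 h before and 1 h after the dose. On its natural reading the question about the last meal is anchored to the visit, not to the dose. Routine draws can fall hours after the dose, so one or more meals may lie in between and hide the relevant one.

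There is a second, separate limit. A concentration measured under repeated dosing with a long half-life reflects several days of intake. A food label for one dose, even a correct one, describes only part of what is in the sample.

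At stake is the concentration side of one of the two relations in the primary objective, adherence against plasma concentration. By the article's own figure, food is a large modifier of bioavailability. If it is poorly recorded, its effect stays in the concentration data, including the ratio of measured to model-predicted concentration, as unexplained variance.

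**Working it through.** **Part 1: what the two recorded times can classify.** Inputs: time of last meal, time of last dose, and the 2 h / 1 h rule, all from Blood sample and laboratory test.

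| Position of the last meal | What can be concluded about the last dose |
|---|---|
| Before the dose | Classifiable: no later meal exists, and the 2 h condition can be checked directly |
| Less than 1 h after the dose | Breach shown |
| 1 h or more after the dose | Unknown: a meal in the 2 h before the dose, or an earlier meal within 1 h after it, is not seen |

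Examples (clock times are illustrative):

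- Dose with breakfast at 08:00, visit 10:00. Recorded: dose 08:00, meal 08:00. Correctly shown as a breach.
- Dose with breakfast at 08:00, lunch 12:30, visit 14:00. Recorded: dose 08:00, meal 12:30. Looks compliant but is a breach.
- Dose 08:00, breakfast 09:30, lunch 12:30, visit 14:00. The record is identical to the previous one, but the rule was followed.
- Evening dose 18:30 after dinner at 18:00, breakfast 08:00, visit 10:00. Recorded: dose 18:30, meal 08:00. Looks compliant but is a breach.

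If the third row of the table is coded as compliant, the error runs one way: fed doses are counted as fasted, never the reverse.

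The frequency depends on dosing and visit times that the article does not give. As an illustration only, assume meals at about 08:00, 12:30 and 18:00, visits spread evenly from 09:00 to 16:00, 30% of doses taken with food, and the third row coded as compliant. A simulation then detects 50% of fed last doses if everyone doses in the morning, 38% if 75% do, 25% if half do, and 0% if everyone doses in the evening. No compliant dose is flagged wrongly in any of these. The figures show the range that the schedule can produce; they are not an estimate for this study.

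**Part 2: how much of the sample the last dose explains.** Inputs: half-life 36 h (Pharmacokinetics); dosing interval 24 h, an assumption drawn from "after administration of 150 mg a day" in the same section; food ratio R = 1.8 to 2.0, taken as the range for an effect described as almost two-fold; a one-compartment model at steady state.

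Share of the trough from the last dose: s = 1 - 2^(-24/36) = 1 - 0.63 = 0.37. Earlier doses supply the remaining 0.63.

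Concentration relative to all doses fasted:

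| Pattern | Formula | R = 1.8 | R = 2.0 |
|---|---|---|---|
| Only the last dose fed | 1 + s(R - 1) | 1.30 | 1.37 |
| All doses except the last fed | R - s(R - 1) | 1.50 | 1.63 |
| All doses fed | R | 1.80 | 2.00 |
| Last dose missed, rest fasted | 1 - s | 0.63 | 0.63 |

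The second row is the telling one. A patient who usually eats with the dose but happened not to on the last occasion would be labelled fasted, correctly for that dose, while the concentration is raised by about 50% to 63%.

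The article's only design figure, 65 patients, has no bearing on this check.

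**The case against.** The best reply is that the two times are informative in two of the three situations, and that the article fixes no coding rule. That stands. A reader might infer that the questions cannot show food intake at all, or that patients will be misclassified. The text supports neither: an analyst could code the third situation as unknown, and misclassification follows only if it is coded as compliant.

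It can also be said that this is a one-line summary in a condensed article, and that the actual question may be framed around the dose. That is possible. But if the last meal means the last one before the dose, a meal shortly after the dose goes unseen, so either reading leaves one side of the rule unobserved.

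Two stronger readings should be resisted. The first is that the food effect exceeds the adherence effect. That sets every dose taken with food (up to 2.0 times) against one missed dose (-37%). Dose for dose the figures are +30% to +37% against -37%, so food could offset a missed dose at most. A recently missed dose is also partly visible from the last-dose time, the documented sample time and the electronic monitor. The second is that food and missed doses cancel and so bias the primary relation. That needs patients who neglect the meal instruction also to miss doses. Nothing in the article supports or excludes this link; without it, unrecorded food intake mainly adds noise.

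Finally, the point does not touch how adherence itself is measured, nor the measurement of the adherence-side-effects relation.

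**Conclusion.** The point holds in a limited form. The item as described does not in general deliver the variable that the analysis is meant to use: when the last meal came 1 h or more after the dose, the status of the last dose is undetermined, and nothing else described in the article resolves it. Even a correct label for the last dose covers only about 37% of the steady-state trough and can miss a rise of about 50% to 63% from earlier fed doses. The consequence is unexplained variance in the concentration data behind the adherence-concentration objective. Bias in that relation would require meal adherence and dose adherence to be correlated, which is an assumption.

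The sizes rest on once-daily dosing, a one-compartment model at steady state and a food ratio of 1.8 to 2.0. How many patients are affected cannot be stated from the article. This is a cheap improvement, not an error that invalidates the design.

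**What to change.** At each of the three sampling visits, replace the single last-meal question with:

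1. the time of the last meal before, and of the first meal after, the last erlotinib dose;
2. on how many of the past 7 days the dose was taken outside the meal instruction.

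Keep the last-dose time and the sample time as they are. Derive the food covariate from these answers, and code cases that remain unresolved as unknown, not as compliant. The instruction given to patients is not affected.

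The cost is two short questions in place of one at visits that already take place, with a slight recall burden. The 7-day answer will carry recall error of its own. Treatment, sampling and sample size do not change.

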### Erlotinib

Erlotinib (Tarceva^®^) is an oral anticancer agent, which is registered for the second- and third-line treatment of NSCLC since 2006 [31] Erlotinib is a tyrosine kinase inhibitor (TKI) of epidermal growth factor receptor (EGFR-TKI).

Diarrhea and skin rash are the most common side-effects of erlotinib. The incidence and severity of diarrhea seems to be related to the schedule and dose of erlotinib [32]. Rudin et al [33] have not observed a relationship between the Area Under the Curve (AUC) concentration and diarrhea. However, they did find a relationship between trough plasma concentration (C_trough_) of erlotinib and skin rash. Hidalgo et al [32] also detected a relationship between AUC and skin rash. Interestingly, patients who experienced skin rash had significantly longer survival [34,35].

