### Statistics

The data will be described by means of frequency analysis. Correlation coefficients will be calculated for relationships between adherence, patient characteristics, disease characteristics, side effects, quality of life, patient beliefs and attitude towards disease and medication, dose adjustments and plasma concentration of erlotinib in patients with NSCLC. In particular, the correlation coefficient between plasma concentration and side-effects; the relationship between dose and plasma concentration in daily practice; the influence of different factors on adherence; the influence of different factors on side-effects; the influence of different factors on quality of life; the influence of different factors on dose adjustment and discontinuation. By the use of a multivariate regression analysis the influence of adherence (dependent variable) on plasma concentration and the influence of side-effects (dependent variable) on adherence will be calculated. The dependent variables will be adjusted for potential confounders. For all analyses a two-tailed significance level will be 0.05, all p values below this level will be considered statistically significant. The statistical analyses will be performed with SPSS 15.0 (SPSS Inc. Chicago, Illinois, USA).

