## Discussion

The present study aims to get more insight into patients' experiences with the use of erlotinib in daily practice. We expect variability in the adherence in the general oncology population. This may be complicated by the inter-patient variability in the pharmacokinetics. We hypothesize that side-effects play an important role in the way patients use erlotinib. Therefore, the relationship between self-reported side-effects and adherence is also defined as a main objective. To get more insight into other factors related to adherence and other aspects of the use at home, the effects of determinants are studied in an explorative manner.

We expect that the present study will provide valuable knowledge on patients' experiences with the use of erlotinib. This knowledge will be useful for health care professionals to develop specific interventions to support patients thus improving the adherence and persistence with the use of erlotinib in order to derive optimal benefit from the medication.

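### The planned adherence-concentration analysis does not separate between-patient from within-patient variation, so clearance left unexplained by the covariates can confound it and usually weakens it

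*Protocol article*

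**What the plan says.** The first half of the primary objective is the relationship between adherence and erlotinib plasma concentration; the second half is the relationship between adherence and side-effects (Objectives).

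- **Comparison.** Blood sample and laboratory test plans one plasma sample at each of three visits (weeks 3-4, 8-9 and 15-16). AUC, Cmax, trough and CR come from a population model and "will be compared with the data on adherence from the questionnaires and the electronic monitoring system to study the relationship between adherence" and concentration. CR is the measured level over the model's population prediction. The model inputs are gender, albumin, bilirubin, alpha1-acid glycoprotein, creatinine clearance and smoking. Interacting co-medication is examined as a covariable, and meal timing is recorded.
- **Method.** Statistics says "Correlation coefficients will be calculated for relationships between adherence, patient characteristics" and the other variables. It adds a multivariate regression for "the influence of adherence (dependent variable) on plasma concentration", with adjustment for unnamed potential confounders. It does not say how the three samples per patient enter.
- **Links between the variables.** Erlotinib cites one study that related trough level to skin rash and another that "also detected a relationship between AUC and skin rash". Causes of non-adherence lists side-effects among the factors associated with non-adherence. The Discussion states: "We hypothesize that side-effects play an important role in the way patients use erlotinib". On the expected variability in adherence, it adds: "This may be complicated by the inter-patient variability in the pharmacokinetics".

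**The concern.** Put together, these statements describe a common cause. A patient who clears the drug slowly has a higher level at any given adherence. If the higher level brings more side-effects and these lead to missed doses, that patient has a high level and poor adherence. This works against the effect of interest, in which more doses taken give a higher level. It operates even when every patient is prescribed the same dose.

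CR removes only the part of clearance that the covariates predict. The remainder is not observed, so it cannot be entered as a confounder. Entering side-effects measured at the same time is not a clean substitute, because they are themselves a consequence of the level.

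At stake is the reading of the first primary result. A weak correlation across patients could be reported as showing that adherence matters little for plasma level, although each missed dose lowers it.

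**Working it through.** **The plan's own figure.** The article states: "According to the sample size calculation (see Statistics) a number of 65 patients will be enrolled". The Statistics section gives no effect size or power, so 65 cannot be reproduced. For orientation, with "For all analyses a two-tailed significance level will be 0.05", Fisher's z gives a detectable correlation of tanh((1.960 + 0.842)/sqrt(62)) = 0.34 at 80% power.

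**Inputs**
- Between-patient spread: Pharmacokinetics gives Cmax 1.737 ± 0.777. Taking ± as an SD, CV = 0.777/1.737 = 0.447 and log-SD s = sqrt(ln(1 + 0.447²)) = 0.427. This is a stand-in for the spread of clearance.
- Assumed, because the documents give no value: level proportional to doses taken (true log-log slope 1); r1, the link from exposure to side-effects; r2, the link from side-effects to lower adherence; SD_A, the between-patient SD of log adherence; R, the share of clearance variance that the covariates explain.

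**Between-patient slope.** Log level = log adherence − log clearance. The two links give log clearance and log adherence a correlation of r1·r2. After covariate correction their covariance is r1·r2·SD_A·s·(1 − R), so

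slope = 1 − r1·r2·s·(1 − R)/SD_A.

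Example: r1 = r2 = 0.35, SD_A = 0.10, R = 0 gives 1 − 0.1225 × 0.427/0.10 = 0.48.

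| r1 = r2 | SD_A | R = 0 | R = 0.3 | R = 0.6 |
|---|---|---|---|---|
| 0.2 | 0.10 | 0.83 | 0.88 | 0.93 |
| 0.2 | 0.20 | 0.91 | 0.94 | 0.97 |
| 0.35 | 0.10 | 0.48 | 0.63 | 0.79 |
| 0.35 | 0.20 | 0.74 | 0.82 | 0.90 |
| 0.5 | 0.10 | −0.07 | 0.25 | 0.57 |
| 0.5 | 0.20 | 0.47 | 0.63 | 0.79 |

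At R = 1, or if either link is zero, the slope is 1. If side-effects raised adherence, the bias would be upward: links of 0.3 give 1 + 0.09 × 0.427/0.10 = 1.38 at SD_A 0.10, and 1.19 at 0.20.

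A separate simulation, in which side-effects respond to the actual level, agrees: 0.83, 0.61 and −0.13 for links of 0.2, 0.3 and 0.5 at SD_A 0.10 without correction. A three-visit version, with adherence reacting to side-effects at the previous visit, gave patient-mean slopes of 0.76, 0.41 and −0.79. Averaging the three samples therefore does not help. Adjusting for same-time side-effects left slopes of 0.75 to 0.99 when both links were present and part of clearance stayed unexplained.

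**Correlation and power at n = 65** (r1 = r2 = 0.35, R = 0)
- SD_A 0.10: without feedback, r = 0.10/sqrt(0.01 + 0.1824) = 0.23 and power is 45%. With feedback, r = (0.01 − 0.00523)/(0.10 × 0.4265) = 0.11 and power is 14%.
- SD_A 0.20: r falls from 0.42 to 0.33, and power from 95% to 77%.

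**Within-patient slope** (65 patients, three samples, residual log-SD 0.25, r1·r2 = 0.1225, SD_A 0.10)
- No feedback within patients: slope 1.00. Its standard error is about 0.25/(sqrt(130) × SD within): 0.31 if the within-patient adherence SD is 0.07, and 0.73 if it is 0.03. Simulation gave 0.32 and 0.74 to 0.75.
- Suppose instead that the residual is real exposure and adherence reacts to it at the same rate, 0.1225 × 0.10/0.427 = 0.0287 per log unit, with within-patient SD 0.07. The covariance is then 0.0287 × 0.0625 = 0.00179.
  - Reaction in the same interval: 1 − 0.00179/0.0049 = 0.63 (simulated 0.64 to 0.65).
  - Reaction at the next visit: 1 + (2/3) × 0.00179/(2 × 0.0049) = 1.12 (simulated 1.12 to 1.13).

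**The case against.** **The across-patient analysis is inferred.** The article names correlations and a regression and does not rule out a within-patient analysis; a fuller plan may contain one. This stands as a limit. What remains is that the article does state its exposure measures, methods and confounder strategy, and that strategy cannot reach unobserved clearance.

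**The sign is not in the hypothesis.** The Discussion says side-effects play a role in how patients use the drug, not in which direction. The negative sign comes from Causes of non-adherence. One cited study saw no link between AUC and diarrhea, and rash is linked with longer survival, which could encourage adherence. This also stands, so the claim must be conditional.

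**The bias may be small.** The model uses six covariates, co-medication is examined, and adherence may vary widely. With weak links and good covariates the slope is 0.93 to 0.97. A reader might infer a planned relationship biased to zero or below. The documents do not support that: among the cases tabulated, a negative slope appears only with links of 0.5, narrow adherence spread and no covariate correction.

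**The within-patient coefficient has its own faults.** Pharmacokinetics says food and co-medication shift levels, so visit-to-visit differences can be real exposure to which patients react. The figures of 0.63 and 1.12 above show the consequence. A reader might take the deviation coefficient as the effect of adherence; that goes too far.

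**It is partly acknowledged.** The Discussion mentions variability in pharmacokinetics, but draws no consequence for the analysis.

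**Conclusion.** The concern holds in conditional form. If higher exposure causes more side-effects and side-effects lower adherence, clearance not explained by the covariates confounds the between-patient relationship and usually attenuates it. The correlation and regression as written do not separate that relationship from the within-patient one.

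For assumed links of 0.2 to 0.35 and a log-adherence SD of 0.10 to 0.20, a true slope of 1 would appear as roughly 0.5 to 0.9 before covariate correction, and nearer 1 the more the CR covariates explain. These are illustrations: the documents give neither the link strengths, nor the adherence spread, nor the share of clearance explained. The low power at narrow adherence spread is only partly due to this bias, since it is already 45% without it.

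**What to change.** In Blood sample and laboratory test and in Statistics:

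1. Make log CR (or log concentration) the outcome. Statistics currently labels adherence the dependent variable.
2. Enter cap-measured adherence before each of the three samples, using only cap data that precede the sample, split into the patient's own mean and the deviation from that mean. A random intercept without this split blends the two slopes: in simulation it gave 0.88 when the within-patient adherence SD was 0.07 and 0.68 when it was 0.03.
3. Include the meal timing and co-medication already recorded.
4. Report both coefficients with confidence intervals. State that the between-patient coefficient is open to confounding by individual clearance, and that a weak between-patient correlation does not show that adherence leaves plasma level unaffected.

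The cost is analysis wording; the data are already planned. The within-patient coefficient is imprecise if adherence varies little within patients, gains nothing from patients with one sample, and is itself biased if adherence reacts to short-term changes in exposure. For that reason neither coefficient should be declared the effect on its own.
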